### Ethical aspects

This is a pragmatic clinical trial conducted under real-world clinical practice conditions. The pharmaceutical intervention under study is part of the primary care pharmaceutical services.

Patient data will be extracted from the Electronic health record by the Department of information systems. The principal investigator (PI) will work with a dataset derived from this extraction, in which patient information will be pseudonymized. Pseudonymization process will be carried out by the Department of information systems. This department will generate and send a code–patient identity correspondence document to the responsible clinician, exclusively for the purpose of facilitating the shared decision-making process. PI will not have access to the document linking patient identity to the pseudonymized codes, ensuring compliance with data protection and confidentiality standards. Portfolio and is being evaluated during its implementation process in routine clinical practice.

In all cases, it is the responsibility of the treating physician to evaluate the applicability of the recommendations generated by the medication review, based on clinical judgment and in consultation with the patient. As a safeguard against potential harm, a criterion for exclusion was that the physician considered participation potentially detrimental for the patient. Patients in the control group facilities received the pharmaceutical intervention after the study follow-up period, according to the planned implementation process.

The study was designed in accordance with the Good research practice guidelines in health sciences of the Catalan health institute (Institut Català de la Salut, 2010), the principles of the Declaration of Helsinki (2013 revision), and applicable regulations.

The protocol was reviewed and formally approved by the Clinical research ethics committee (CEIC) of IDIAP Jordi Gol (Barcelona), including the formal exemption from informed consent for patients.

## Discussion

This is a pragmatic study that integrates an evaluation framework into the implementation process of a new medication review and optimization program in nursing homes. Although the intervention is well-established and supported by scientific evidence, the main goal of this study is to assess its utility and effectiveness in routine clinical practice.

A novel aspect of the program is the expanded role of the clinical pharmacist as a support and advisor to general practitioners in identifying drug-related problems and proposing solutions. This approach aligns with healthcare improvement initiatives in nursing homes, involving a redefinition of professional roles and the promotion of multidisciplinary teamwork (Departament de Salut, 2019).

This study will have certain limitations that should be considered when interpreting the results. One of the main concerns will be the non-random allocation of care homes to the intervention and control groups, which was based on convenience and collaboration feasibility within the framework of the local pharmaceutical review program. Although this approach is justified for practical reasons, it may introduce a potential risk of selection bias. To minimize this, we will ensure that the two groups are comparable at baseline in terms of care home characteristics (e.g., geographical location, size, and organizational structure) and patient-level variables (e.g., sociodemographic and clinical profiles, as well as the quality of pharmacotherapeutic plans). Any residual imbalances will be addressed through appropriate statistical adjustments during the analysis.

The fact that the assessment is neither blind nor independent introduces a potential risk of information bias, as the pharmacists responsible for implementing the intervention also carry out the outcome assessments in the intervention group. However, this risk is mitigated by the fact that outcome data will be obtained directly and systematically from the electronic health records, based on structured variables that are not modifiable by the assessors. Due to resource limitations, it is not feasible to separate intervention and assessment roles, and this potential bias should be considered when interpreting the study results.

According to a meta-analysis evaluating pharmacist-led interventions within multidisciplinary teams (physician, nurse, pharmacist) in nursing homes, such interventions led to a reduction of 2.2 DRPs (0.28–4.12; I^2^ = 44%, p = 0.02) based on the MAI criteria, a mean reduction of 1.9 medications, and an intervention acceptance rate of 69.8% (Lee et al., 2019).

The results of this study will inform the real-world utility and feasibility of the evaluated intervention and its implementation process, including the evolving role of the primary care pharmacist within a multidisciplinary team. This information will be valuable in refining the medication review program and optimizing its practical implementation.

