### Intervention

The intervention involves a systematic and structured review of patients’ pharmacotherapeutic treatment plans to identify problems or risks associated with their medication regimens and propose changes or improvements. This procedure is part of the standard service portfolio of the regional healthcare authority and is conducted by pharmacists from the territorial Primary Care Pharmacy Unit. The intervention is based on the protocol outlined in the document “Rational use of medicines. Basic medication management in chronic patients: Reconciliation, review, desprescription, and adherence (Departament de Salut, 2013).

The review process includes two phases. In the first phase, individual pharmacological treatment plans are reviewed to identify DRPs, which are classified into four types: indication-related, appropriateness, effectiveness, and safety issues. Indication-related DRPs include medications. Without a current indication or missing necessary medications.

Appropriateness-related DRPs assess dosage, frequency, regimen, and duration, as well as the suitability of medications based on age, renal and hepatic function, and other clinical parameters. To identify potentially inappropriate medications by age group, we used the reference “Potentially inappropriate medications for the elderly” (Servei Català de la Salut, 2020), which integrates the Beers Criteria (American Geriatrics Society Beers Criteria Update Expert Panel, 2019), STOPP-START criteria (O'Mahony et al., 2015), Priscus List (Holt et al., 2010), and EU-PIM List (Fick et al., 2015), providing justification, recommendations for change and the criteria on which these recommendations are based. Effectiveness-related DRPs assess therapeutic outcomes in relation to clinical goals and identify instances of overtreatment or the need for de-intensification based on the patient’s health status.

Safety-related DRPs include therapeutic duplications, contraindications, adverse effects, allergies, drug interactions, or insufficient laboratory monitoring.

In the second phase, pharmacists issue proposals to optimize pharmacotherapy in response to identified DRPs. Recommendations may include discontinuation, substitution, therapeutic equivalents, initiation of new treatments, dosage or frequency adjustments, or enhanced monitoring.

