### Measurement

Data were collected at baseline and at 3 months using the electronic prescription module of each patient’s electronic health record. The evaluation was conducted by the pharmacist implementing the intervention, who was not blinded to the study group allocation of nursing homes and patients (Table 1).➢ Outcome variables

**TABLE 1 T1:** Variables and measuring instruments.

Variable	Instrument	Application time	
		Basal	3 months
Sociodemographic variables	Questionnaire *ad hoc*	X	
Age			
Sex			
Length of time living in the nursing home			
Pharmacotherapeutic plan			
Description of the pharmacotherapeutic plan	ATC classification^a^	X	
Description and classification of the DPRs^b^ detected	Classification	X	
Clinical			
Comorbidity			
*Physical comorbidity*	Checklist	X	
*Psychiatric comorbidity*	Checklist		
*Global indicator*	*Charlson index*	X	
Complex Chronic Patient^c^	Checklist	X	
Advanced Chronic Care Model^c^	Checklist	X	
Functional capacity	Barthel index	X	
Cognitive status	SPMSQ^d^ Pfeiffer		
Clinical Results			
Drug related problems (DRP)^b^	Questionnaire *ad hoc*	X	X
*Number of DR P* ^b^ *per patient*			
*Proportion of patients with DRP*			
Polymedication	Questionnaire *ad hoc*	X	X
*Number of drugs a patient receives simultaneously*			
*Number of polymedicated patients*			
Results of the pharmaceutical review (only in the intervention group)			
Proposals for change	Questionnaire *ad hoc*	X	
Proposals implemented	Questionnaire *ad hoc*		X

^a^
ATC: anatomical therapeutic chemical classification system.

^b^
DRP: drug related problems.

^c^
According to the criteria of *Bases per a un model català d’atenció a les persones amb necessitats complexes. Conceptualització i introducció als elements operatius. Generalitat de Catalunya, 2017.*

^d^
SPMSQ: short portable mental status questionnaire.

Drug-Related Problems (DRPs) were quantified as total number, DRPs per patient, and the proportion of patients with at least one DRP. DRPs were classified into four categories: indication, appropriateness, effectiveness, and safety (Table 2).

**TABLE 2 T2:** List and classification of drug-related problems (DRP) considered in this study.

Category	DRP
Indication	- Medically unnecessary/not indicated/not appropriate for the health problem - Failure to prescribe a necessary medicine
Adequacy	- Medically inappropriate - Dose higher or lower than correct dosage - Incorrect administration frequency - Wrong drug form - Duration too long or too short

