Effectiveness	- Failure to achieve the therapeutic goal - The goal is achieved but the intensity of the pharmacological treatment needs to be reduced - Not the most effective alternative based on evidence and/or clinical practice guidelines
Safety	- Allergy or adverse effect - Contraindication - Therapeutic duplication - Drug- drug interaction - Lack of analytical controls

This classification is based on the position statement of the Spanish Society of Primary Care Pharmacists (*Sociedad Española de Farmacéuticos de Atención Primaria*) (Socied ad Española de Farmacéuticos de Atención Primaria SEFAP, 2022).

Polymedication was measured as the number of medications taken concurrently by each patient and the number of polymedicated patients. Polypharmacy was defined as the chronic use of ≥10 medications (Duerden et al., 2013; Gnjidic et al., 2012). Topical treatments, eye drops, occasional treatments, and those used for acute conditions were excluded from this count. Fixed-dose combinations were counted according to the number of active ingredients. Multiple dosages of the same active ingredient were counted as one drug.➢ Secondary variables

Sociodemographic variables such as age and sex were collected. Regarding the pharmacotherapeutic plan, the number and classification of DRPs identified (by indication, appropriateness, effectiveness, or safety) were recorded.

Clinical variables included physical comorbidity, such as the presence of chronic conditions like diabetes, cardiovascular disease, respiratory disease, dementia, and cancer. Psychiatric comorbidity included diagnoses of depression, anxiety, psychotic disorders, and substance use disorders.

Comorbidity was also quantified using the Charlson Comorbidity Index (Charlson et al., 1987), which integrates age and 19 clinical conditions to provide a summary score correlated with 1-year and 10-year survival.

To assess chronic care complexity, we recorded the number of patients identified as Complex chronic patients (PCC) or as part of the Advanced chronic care model (MACA) (Departament de Salut, 2017). PCCs are defined by clinicians as having complex clinical management needs due to multimorbidity, a polypharmacy, clinical instability, resource use, and age extremes. MACA patients are those with a limited life expectancy and palliative care needs.

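### The stated safeguard against unblinded assessment suits drug counts but does not hold for the composite DRP outcomes, on which the trial is sized

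*Protocol article*

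**What the plan says.** The Discussion of the protocol article names a risk of information bias, because "the pharmacists responsible for implementing the intervention also carry out the outcome assessments in the intervention group". It then offers a mitigation: "outcome data will be obtained directly and systematically from the electronic health records, based on structured variables that are not modifiable by the assessors". It adds that resources do not allow the two roles to be separated, and asks readers to keep the bias in mind.

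The Measurement section describes the assessor in wider terms: "The evaluation was conducted by the pharmacist implementing the intervention, who was not blinded to the study group allocation of nursing homes and patients". It gives the electronic prescription module as the data source. Table 1 lists an ad hoc questionnaire as the instrument for both the DRP and the polymedication outcomes, at baseline and at 3 months.

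The Intervention section explains how DRPs arise: "individual pharmacological treatment plans are reviewed to identify DRPs, which are classified into four types". For one of the types it says: "Effectiveness-related DRPs assess therapeutic outcomes in relation to clinical goals and identify instances of overtreatment or the need for de-intensification". Table 2 includes items such as "Not the most effective alternative based on evidence and/or clinical practice guidelines".

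The Statistical method section names four primary outcomes: DRPs per patient, proportion with DRPs, drugs per patient and proportion polymedicated. The Sample size section is built on the proportion with DRPs.

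**The concern.** The mitigation depends on the outcome value already being in the record before the assessor arrives. A prescription is there. A DRP, in general, is not: it is the assessor's conclusion about that prescription in that patient. The assessor therefore cannot alter the raw data but does determine the outcome.

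The assessor also knows the group and delivers the intervention, so any leniency at 3 months could differ between arms. Neither the mixed models nor adjustment for baseline imbalance removes differential misclassification of the 3-month outcome. A reader who accepts the mitigation would give a DRP result the same protection as a drug count, although it has less.

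**Working it through.** **1. The plan's own figure.** Inputs from Sample size: 0.50 against 0.40, two-sided alpha 0.05, power 0.80, ICC 0.001, 12 clusters of 37 per group, 10% loss.

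- Per group before clustering: [1.960 × √(2 × 0.45 × 0.55) + 0.842 × √(0.50 × 0.50 + 0.40 × 0.60)]² / 0.10², which rounds up to 388.
- Design effect: 1 + (37 − 1) × 0.001 = 1.036, and 388 × 1.036 = 402.
- With loss: 402 / 0.90 = 447 per group, or 447 / 12 = 37.25 per home.

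The stated 12 × 37 = 444 per group reproduces to within 3 patients. The trial is therefore sized on a difference of 10 percentage points in the proportion with DRPs.

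**2. The safeguard set against each outcome.**

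- *Number of drugs and polypharmacy (10 or more).* These can be counted from prescriptions under stated rules for combinations, topical products and repeat strengths. A little discretion remains, for instance over what is an occasional treatment. The safeguard largely fits.
- *DRPs that can be checked against records.* Therapeutic duplication, drug-drug interaction and drugs on the cited list of potentially inappropriate medicines can largely be derived from data. The safeguard fits in part.
- *DRPs that need judgement.* No current indication, a necessary drug missing, goal not reached, treatment to be de-intensified, a more effective alternative available. These require a clinical conclusion. The safeguard does not fit.

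The two DRP primary outcomes pool the second and third groups, so the composite does not have the claimed property. The Introduction itself cites a study in which pharmacists found DRPs that other professionals had missed, which suggests that detection depends on who looks.

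**3. How much misclassification would matter.** This is an illustration; its assumptions are not in the documents. Suppose that true prevalence at 3 months is 50% in both arms, that the intervention has no effect, and that control patients are classified correctly. Let f be the share of intervention patients with at least one DRP who are classified as having none, that is, with all their DRPs unrecorded.

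- Observed intervention prevalence: p = 0.50 × (1 − f). Bias: 0.50 × f.
- Effective number per group: 444 × 0.90 = 399.6 followed up, or 33.3 per home; 399.6 / (1 + (33.3 − 1) × 0.001) = 387.1.
- Chance of a significant result favouring the intervention, with p̄ = (0.50 + p)/2: Φ{[0.50 − p − 1.960 × √(2p̄(1 − p̄)/387.1)] / √([0.25 + p(1 − p)]/387.1)}.

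| f | Observed p | Bias (points) | Chance of a favourable significant result |
|---|---|---|---|
| 0% | 50.0% | 0 | 2.5% |
| 5% | 47.5% | 2.5 | 10% |
| 10% | 45.0% | 5.0 | 29% |
| 15% | 42.5% | 7.5 | 55% |
| 20% | 40.0% | 10.0 | 80% |

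This is a two-proportion approximation using the plan's ICC, not the mixed logistic model that the plan will fit.

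**4. Who assesses the control homes.** Measurement gives the evaluation to the implementing pharmacist without limiting it to one arm. The Discussion says that these pharmacists "also carry out the outcome assessments in the intervention group" and does not say who assesses control patients.

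**The case against.** Much of the case for the protocol stands.

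- *The bias is disclosed.* The article states the lack of blinding twice, names information bias, says why roles cannot be separated and closes with a caveat. It claims mitigation, not removal. A reader might infer concealment; the text does not support that.
- *Some DRP types are anchored in records.* A reader might conclude that the safeguard is false for every DRP. That goes too far: the recorded prescriptions limit what an assessor can report, and a published list governs part of the review. The failure concerns the composite.
- *The ad hoc questionnaire proves little.* Table 1 gives the same instrument for drug counts and sociodemographic data, so the label does not separate judged from extracted outcomes. The argument rests on the DRP definitions instead.
- *Different assessors by arm are not shown.* The two descriptions differ, which calls for reconciliation and no more.
- *Rejected proposals.* A reader might infer that a DRP stops being counted once the committee or patient rejects the proposal. Nothing says so; the article says only that proposals may be rejected, and Table 1 records implementation separately.
- *The 20% is chosen to reproduce the planned effect.* It is not an estimate. It is also demanding: the binary outcome changes only if every DRP in a patient goes unrecorded, and the Introduction cites averages of 2.2 to 4 per patient.

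What remains is that the reason given for mitigation does not apply to the judged part of two primary outcomes.

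**Conclusion.** The concern holds in a limited form. The property claimed in the Discussion is largely right for number of drugs and polypharmacy and wrong for the composite DRP outcomes, which are two of the four primary outcomes and include the one used for sample size. The contradiction lies within the article and needs no outside figure.

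The size of any resulting bias is unknown. Under the stated assumptions, each 5% of DRP-positive intervention patients classified as DRP-free moves the observed difference by 2.5 points, and 20% reproduces the planned 10 points with no true effect. This shows how sensitive the outcome is; it is not evidence that such misclassification will occur, or that it would run in this direction.

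**What to change.** 1. In the Discussion, limit the statement about structured, unmodifiable variables to number of drugs and polypharmacy, and say that for DRPs the data source does not mitigate the information-bias risk.
2. Reconcile Measurement and Discussion on who assesses DRPs in control homes. Use the same assessors, form and phase-one review criteria in both arms at both dates, and count a DRP by those criteria whether or not the proposal was accepted.
3. Add a pre-specified sensitivity outcome made of the DRP types that can be computed from the extracted data, such as listed potentially inappropriate drugs, therapeutic duplication and drug-drug interactions. Include missing laboratory monitoring only if laboratory data are extracted. Run identical code in both arms and at both dates and report the result beside the judged outcome. Read any disagreement as possible assessment bias; it should not act as a gate on the conclusion.

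The cost is some wording and some programming on the extraction already planned with the information-systems department. The computed outcome covers only part of Table 2, so the two outcomes may also differ for that reason. Hiding home and date from the existing assessors is optional and of limited value, since they may recognise plans that they reviewed.

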## Data Availability

The original contributions presented in the study are included in the article/supplementary material, further inquiries can be directed to the corresponding author.
